### Methods

Our primary outcome will be unplanned emergency hospital admissions (outcome 1), secondary outcomes will include: Accident & Emergency (A&E) attendances (outcome 2), 30-day readmission rates (outcome 3), admission to nursing/residential care home (outcome 4), and mortality (outcome 5). The study will analyse the seasonal impacts on hospital admissions during winter.

The study will use quasi-experimental methods and apply two complementary causal approaches: (i) inverse probability of treatment weighted difference-in-differences (IPTW-DiD) (Bettega et al., 2024; Chesnaye et al., 2022; Wei et al., 2023), this is our primary approach to robustly estimate causal effects of telehealth interventions using routinely collected data de-identified by Mersey Care between 2018 and 2024; (ii) To strengthen causal identification, we will also implement regression discontinuity (RD) designs (Thistlethwaite and Campbell, 1960), which are widely adopted in health research (Calonico et al., 2024; Thapa et al., 2025), based on eligibility thresholds derived from the Johns Hopkins ACG risk score (NHS England, 2025d), this is our secondary confirmatory approach. This aspect of the analysis is subject to the availability of Johns Hopkins data. MCTS is commissioned to provide daily care to up to 2,000 patients in Liverpool, 50 patients in Sefton, 100 patients in St Helens, 100 patients in Wirral, and 100 patients in Chesire, respectively. Since the service has not been available over the period to all groups in all parts of Cheshire and Merseyside to construct an appropriate comparator group who did not receive the telehealth service but had similar characteristics (confounders and pre-intervention outcomes) to the patients that did receive it (Barr et al., 2022).

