The primary exposure is active enrolment onto the MCTS. Referral alone will not constitute exposure, as not all referred patients commence telehealth monitoring. For enrolled patients, the index date will be defined as the date on which active telehealth monitoring begins. To account for temporal variation in healthcare utilisation and service delivery, telehealth enrolment dates will be grouped into calendar quarters (Q1: January–March; Q2: April–June; Q3: July–September; Q4: October–December). Comparator patients will be selected from quarterly eligibility snapshots comprising individuals who were eligible for MCTS, alive, and registered during the same quarter but who did not enrol onto the service. Calendar quarter will be used as an exact matching variable within the propensity score matching process, ensuring that telehealth participants are compared only with eligible non-enrolled patients observed during the same time period. Additional demographic, clinical, risk, and baseline healthcare utilisation variables will be incorporated into the matching procedure. This approach aims to minimise temporal bias arising from changes in healthcare utilisation, seasonal pressures, COVID-19 recovery effects, admission practices, and service delivery over the study period. The primary analysis will therefore estimate the effect of active enrolment onto MCTS compared with eligible non-enrolment during the same calendar quarter. Findings should be interpreted as representing the effect of the telehealth service model as delivered in routine practice rather than the effect of referral alone or any individual intervention component.

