### Data

The study will use a cohort of monthly data from the Cheshire and Merseyside Secure Data Environment (CM-SDE), the NHS secure data environment that includes linked data across health and care services for all patients registered with a GP in Cheshire and Merseyside. We will use CM-SDE covering a period, 2018–2024 including linked data from the following datasets:

NHS

Primary care dataPrimary care prescribing dataTelehealth services data from the MC telehealth case management system.Secondary care data—Admitted Patient Care (SUS-APC)Community Services Data Set (CSDS)Mental Health Services Data Set (MHSDS)Emergency Care Data Set (ECDS)

Local Authority Adult Social Care

Adult Social Care Dataset (ASCD)

Open data—linked to Lower layer super output areas (LSOAs)

Indices of deprivation

All these datasets are available and can be linked within the CM-SDE. Patient characteristics will reflect individuals at the time of receiving telehealth service and so will correspond to the latest measurement taken during the study period 2018–2024. Table 2 summarises the details of outcome and exposure variables, definition criteria, and datasets from which the variable is derived that would be used in WP1 of the study.

**Table 2 TB2:** Exposure, covariates, and outcome variables for WP1.

Variable category	Variable	Definition/criteria	Data source
Primary exposure	MCTS enrolment	Active enrolment onto the Mersey Care Telehealth Service (Yes/No)	MCTS service dataset
Demographic and baseline characteristics	Age	Age at index date (≥18 years)	SUS-APC
	Sex	Male, Female, Other	SUS-APC
	Ethnicity	White British, Other White, Black, Indian, Pakistani, Bangladeshi, Chinese, Other Asian, Other ethnic group	SUS-APC
	Living alone	Yes/No	Primary Care
	Living with under-18s	Yes/No	Primary Care
	Household size	Number of people in household	Primary Care
	Geography	LSOA 2011	SUS-APC
	Deprivation	IMD 2019	SUS-APC
	Frailty	Fit, mild, moderate, severe frailty	Primary Care
Clinical characteristics	Long-term conditions	Hypertension, cancer, diabetes, CVD, heart failure, CKD, asthma, COPD, depression, schizophrenia, bipolar disorder	Primary Care
Baseline healthcare utilisation	Emergency admissions (previous 12 months)	Count of emergency admissions before index date	SUS-APC
Outcomes	Unplanned emergency hospital admissions	Count of admissions during follow-up	SUS-APC
	A&E attendances	Count of attendances during follow-up	SUS-ECDS

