	30-day readmission	Readmission within 30 days of discharge	SUS-APC
	Mortality	Date of death during follow-up	Primary Care

**Abbreviations:** IMD—The index of multiple deprivation; A&E—Accident & Emergency; CVD—cardiovascular disease; CKD—chronic kidney disease; COPD—Chronic obstructive pulmonary disease; SUS-APC—Secondary uses service admitted patient care; SUS-ECDS—Secondary uses service emergency care dataset; LSOA—Lower layer super output areas

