### Analysis

The study uses two quasi-experimental methods: IPTW-DiD and RD designs. These methods help to reduce the risk of selection bias due to systematic differences between those receiving and not receiving the intervention, in two ways.

The primary approach of the analysis is IPTW-DiD, which is specifically designed to adjust observed differences by reweighting individuals according to their probability of receiving treatment, thereby approximating a pseudo-population in which treatment is independent of observed confounders. The treated cohort will comprise patients who received telehealth, with treatment timing defined by the first quarter in which telehealth was received; patient-quarter observations from this quarter onwards will be considered post-intervention. For untreated patients, comparable index quarters will be assigned to define the pre- and post-intervention periods.

The initial analytic cohort will be restricted to patients aged 50 years or above with at least one relevant long-term condition linked to the telehealth packages: COPD, diabetes, or HF. These eligibility criteria will be applied to both treated and untreated patients to ensure that the control group comprises individuals with a realistic probability of receiving the intervention. To avoid interpreting unobserved quarters as zero healthcare utilisation, the initial analysis will use a balanced panel of patients observed in all 24 quarters across the 6-year study period. The potential selection introduced by excluding patients who die, move away, or register with a GP partway through the study period will be explored in sensitivity analyses.

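### The lead WP1 cohort keeps only patients observed in all 24 quarters, so inclusion depends on surviving after the index date and the mortality outcome has almost no deaths to compare

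*Protocol article*

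**What the plan says.** In the WP1 Analysis section, "The primary approach of the analysis is IPTW-DiD". The cohort is then fixed: "the initial analysis will use a balanced panel of patients observed in all 24 quarters across the 6-year study period". The reason given is "To avoid interpreting unobserved quarters as zero healthcare utilisation". The section recognises a consequence and leaves it to sensitivity analyses that it does not describe: "The potential selection introduced by excluding patients who die, move away, or register with a GP partway through the study period will be explored". For treated patients, everything from the first telehealth quarter onwards counts as post-intervention; untreated patients are assigned comparable index quarters.

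The WP1 Methods section lists mortality as outcome 5, and Table 2 defines it as "Date of death during follow-up", taken from primary care data. No cohort or model is given for mortality separately from the other outcomes.

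The Methods section also describes how comparators are drawn: from quarterly snapshots of people "eligible for MCTS, alive, and registered during the same quarter" who did not enrol.

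On the data window, the Data section says "We will use CM-SDE covering a period, 2018–2024 including linked data".

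**The concern.** A balanced panel selects on the future. A patient who starts monitoring midway through the window enters the analysis only by surviving and staying registered to its end. Both can be influenced by a service meant to detect deterioration early, so selection could act differently in the two groups.

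Two things are at stake. First, mortality is a named outcome, and the only main cohort described excludes those who have it. Followed as written, the text gives a mortality comparison that is empty or confined to the last quarter. Second, the headline admission estimate would describe people who stayed alive and registered for six years, not those whom the service enrols. It would leave out all decedents' admissions, including those shortly before death, where such a service might show benefit or harm.

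**Working it through.** **1. What the definitions imply.** No assumption is needed here.
- In the panel: observed in quarters 1 to 24.
- Dies in any of quarters 1 to 23: not observed in quarter 24, so not in the panel.
- Dies in quarter 24: may or may not count as observed; the term is not defined.

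Hence outcome 5 has no events in either group before quarter 24. The panel also requires registration from quarter 1, so late registrants are lost too.

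**2. How much could be lost.** The document gives no mortality or deregistration rate, so the annual loss a is assumed.
- Present at the start and still there after 24 quarters: (1 − a)^6.
- For a patient indexed midway, with 12 post-index quarters: (1 − a)^3.
- If all loss is death, the share of that patient's post-index deaths falling in the last quarter: [(1 − a)^2.75 − (1 − a)^3] / [1 − (1 − a)^3].

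| a | kept, 24 quarters | kept, 12 quarters | deaths in last quarter |
|---|---|---|---|
| 2% | 89% | 94% | (0.9460 − 0.9412)/0.0588 = 8.1% |
| 5% | 74% | 86% | (0.8685 − 0.8574)/0.1426 = 7.8% |
| 10% | 53% | 73% | (0.7485 − 0.7290)/0.2710 = 7.2% |
| 15% | 38% | 61% | (0.6396 − 0.6141)/0.3859 = 6.6% |

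So even on the reading most generous to the plan, about 7% to 8% of such patients' deaths could be seen. Measured over all 24 quarters (exponents 5.75 and 6) the share is 3.9% down to 2.5%.

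**3. What happens to the admission rate ratio.** This is an illustrative simulation and every input is assumed except the target of 0.85, which is the protocol's. Frailty is Gamma(1,1) and multiplies both admissions (0.15 per quarter) and death; the index quarter is uniform over quarters 5 to 21; 60% of deaths are preceded by an admission.
- At annual mortality of 8%, 12% and 20%, the rule drops about 20%, 27% and 38% of patients. Hand check at 12%: hazard −ln(0.88) = 0.128 per year over a mean of 3 post-index years gives 0.383, and 1 − 1/1.383 = 28%, against 27% averaged over index quarters.
- Those patients carry about 29%, 39% and 54% of post-index admissions. With less dispersed frailty (gamma shape 5) the shares are about 23%, 32% and 48%. A rerun agreed within two percentage points.
- With a true ratio of 0.85, the survivor-only ratio ranged from 0.83 (mortality hazard ratio 1.2) to 0.88 (hazard ratio 0.7). With no effect on mortality it stayed at about 0.85 to 0.86.
- A second simulation had no effect on admissions and a mortality hazard ratio of 0.6. The panel's pre-period rates were 0.124 (treated) against 0.110 (untreated), compared with 0.150 in both full groups. The post-period ratio alone was 1.12, but the difference-in-differences ratio stayed near 1.0, because frailty was assumed constant over time. Admissions that rise before death would not cancel in this way.

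**4. Is the restriction needed for its stated purpose?** The comparator snapshots already presuppose quarterly knowledge of who is alive and registered, and Table 2 supplies the date of death. Quarters after death or deregistration can therefore be treated as unobserved, not as zero, without discarding the patient.

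**5. The window.** 2018 to 2024 with both end years complete is 7 × 4 = 28 quarters; the panel has 24.

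**The case against.** Several points on the other side stand.

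- The balanced panel is called the initial analysis, not the primary one, and the exclusion is disclosed with sensitivity analyses promised. That is fair. But no other main cohort is named, so this one leads, and the disclosure does not reach the mortality outcome.
- The stated reason concerns utilisation counts, so mortality may be meant for another cohort set out in an analysis plan not shown. That is possible. As the text stands, the only main cohort cannot serve outcome 5 and nothing says that outcome is exempt.
- The snapshots and the panel can be nested: one samples comparators, the other narrows the initial analysis. This is accepted. They define different populations, but they are not a flat contradiction.
- The simulated admission ratio moves little, and an unbalanced panel does not remove the problem. At a mortality hazard ratio of 0.7, the unbalanced analysis with time at risk gave about 0.87 with admissions just before death counted, and 0.88 to 0.91 without them. It was no closer to 0.85 than the survivor panel. This also stands: death remains potentially informative for admissions in either design.

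A reader might infer that WP4 would inherit a cohort without deaths. The document says only that resource use comes from the WP1 question; it does not tie WP4 to the balanced panel. A reader might also infer that the panel ends in late 2023, before the newest locality opened. That follows only if it starts in the first quarter of 2018. If four of the 28 quarters serve as the 12-month look-back, 28 − 4 = 24 and the panel runs to the end of 2024.

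**Conclusion.** The concern holds for mortality and for the target population. The cohort rule conditions on survival and registration after the index date, and it leaves outcome 5 with no deaths before the final quarter in either group. This follows from the definitions alone and should be settled before analysis.

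For emergency admissions, the rule removes decedents' admissions and changes whom the estimate describes. How many patients and admissions are lost depends on assumed mortality. A reader might infer that the primary rate ratio is materially biased; the document does not support that. The size and direction cannot be determined from it, and the simulated shift (0.83 to 0.88 around 0.85) is modest and rests wholly on assumed inputs.

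The 24 against 28 quarters is an ambiguity to clear up, not a proven error.

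**What to change.** 1. Lead with an unbalanced panel built on the quarterly snapshots. Each patient contributes quarters while alive and registered, zero use is coded only in those quarters, and time at risk is the offset.
2. Keep the 24-quarter balanced panel as a sensitivity analysis.
3. Analyse mortality as weighted time to event from the index date, in everyone alive and registered at index. Death has no pre-period, so difference-in-differences does not suit it.
4. State that death is a possibly informative terminal event when the admission rate ratio is interpreted.
5. Give the start and end quarter of the panel once, and reconcile 24 quarters with 2018 to 2024.

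The cost is revised wording and some extra programming, with no new data source: alive and registered status by quarter and date of death are already relied on elsewhere in WP1. The downside is small: death remains a competing event for admissions, so the new lead analysis still needs careful interpretation.

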### Sample

Assuming effective 1:5 average weighting, this gives 19 million patient-months for analysis. Power analysis by simulation (Arnold et al., 2011), accounting for data and model structure indicates that this would be sufficient to estimate a medium effect size (Relative Risk = 0.85)—i.e., 15% relative reduction in the primary outcome attributable to the intervention, with 80% power across these subgroups.

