A treatment model will calculate the likelihood of each patient receiving the intervention using baseline socio-demographic variables, comorbidity measures, and 12-month cumulative pre-intervention healthcare utilisation, such as unplanned emergency admissions. For variables that may change over time, baseline or pre-intervention values will be used. Stabilised IPTW weights (Austin and Stuart, 2015) will be used in the DiD model to balance measured baseline covariates and reduce the influence of extreme weights. Covariate balance, weight stability, overlap/common support, effective sample size, and the plausibility of the conditional parallel-trends assumption will be assessed using weighting diagnostics and pre-intervention outcome trends. Comprehensive sensitivity analyses will be performed to evaluate the robustness of all estimates.

To manage the potentially large untreated population, the above eligibility restrictions will be applied before weighting. If the remaining comparison cohort is still too large for the available computing environment, a 5:1 propensity-score matched comparison cohort based on baseline characteristics may be constructed before applying the weighting approach; this will be reported as a computational sensitivity analysis.

Additionally, the RD design (Thistlethwaite and Campbell, 1960) will serve as a secondary complementary analysis, subject to the availability of a documented Johns Hopkins ACG risk score eligibility threshold (NHS England, 2025d) and sufficient observations close to that threshold. Threshold values, temporal changes, and geographical variations will be documented. As RD estimates a local effect among patients close to the eligibility threshold, its findings will be interpreted alongside, rather than as direct confirmation of, the IPTW-DiD estimates.

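### In WP1, stabilising the weights will not curb extreme weights in the primary difference-in-differences, as the protocol says it will

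*Protocol article*

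**What the plan says.** All of this is in the Protocol article, Work package 1.

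- **Primary method** (Analysis): "The primary approach of the analysis is IPTW-DiD".
- **Weights** (Analysis): stabilised weights "will be used in the DiD model to balance measured baseline covariates and reduce the influence of extreme weights".
- **Treatment model** (Analysis): "A treatment model will calculate the likelihood of each patient receiving the intervention using baseline socio-demographic variables", together with comorbidity and utilisation in the preceding 12 months. It adds: "For variables that may change over time, baseline or pre-intervention values will be used".
- **Exposure** (Data, Table 2): a two-level variable, "Active enrolment onto the Mersey Care Telehealth Service (Yes/No").
- **Checks** (Analysis): "Covariate balance, weight stability, overlap/common support, effective sample size, and the plausibility of the conditional parallel-trends assumption will be assessed", followed by a general commitment: "Comprehensive sensitivity analyses will be performed to evaluate the robustness of all estimates".

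The weights are thus those of a binary point exposure, one per patient and fixed at baseline. Stabilising is the only step that the article names as acting on extreme weights.

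**The concern.** Stabilising is credited with a property that it does not have for weights of this kind. It can help when weights are products over time, as with a time-varying exposure, but no such product is described here. For a single binary exposure it changes the scale of the weights and leaves their spread within each group alone.

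Two things are at stake. First, a team that relies on the sentence may think extreme weights have been dealt with in the primary analysis when nothing has changed. Second, some common summaries improve on stabilising without any real gain. The largest raw weight falls, and effective sample size pooled over both groups can rise sharply, while the estimate and its standard error stay where they were. The article lists effective sample size as a diagnostic but does not say that it is to be read within group.

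**Working it through.** The article gives no figure to reproduce on this point. The check is algebra, followed by simulation with assumed inputs.

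**Algebra.** Let e be a patient's propensity and p the enrolled share.

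- Unstabilised weight w: 1/e if enrolled, 1/(1 − e) if not.
- Stabilised weight: p/e if enrolled, (1 − p)/(1 − e) if not. That is w times a constant c, with c = p for every enrolee and c = 1 − p for every comparator.
- Weighted group mean: Σ(c·w·y)/Σ(c·w) = Σ(w·y)/Σ(w). The constant cancels.
- Within-group effective sample size: (Σ c·w)²/Σ(c·w)² = (Σ w)²/Σ w². It cancels again.
- A group-by-period difference-in-differences is built from four such means, so the estimate is unchanged. Its patient-clustered standard error depends on each patient's share of the group's weight, so that is unchanged too.

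**Simulation 1: group, period and group × period.** The inputs were 20,000 patients, a Poisson count and a relative risk of 0.85 (the effect size in the Sample section). Target enrolled shares of 2%, 5% and 16.7% are assumptions; the last corresponds to 1:5, since 1/6 = 16.7%. A logistic propensity with slope 1.5 per SD of one covariate is also assumed. Where one value is shown, both weights gave it.

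| | 2% | 5% | 16.7% |
|---|---|---|---|
| Enrolees simulated | 382 | 1,003 | 3,234 |
| Estimate | −0.12419 | −0.09347 | −0.04279 |
| Clustered SE | 0.06120 | 0.03892 | 0.01863 |
| Enrolee effective sample size | 35.8 | 147.5 | 536 |
| Largest-to-mean enrolee weight | 54.6 | 50.0 | 85.1 |
| Change on dropping the heaviest enrolee | 0.02036 | 0.00465 | 0.00096 |
| Largest raw weight, unstabilised → stabilised | 2,939 → 56 | 1,016 → 51 | 511 → 83 |
| Pooled effective sample size, unstabilised → stabilised | 139 → 16,696 | 574 → 15,212 | 2,147 → 10,759 |

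Only the last two rows move, and they do not bear on the estimate. The first is pure rescaling: at 2%, 2,938.98 × 0.0191 (the realised share) = 56.1.

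**Simulation 2: 24-quarter panel with staggered index quarters.** The inputs, all assumed apart from the 24 quarters, were 4,000 patients, 10% enrolled and patient fixed effects. Each cell gives unstabilised, then stabilised.

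| Time terms | Estimate | Change on dropping the heaviest enrolee |
|---|---|---|
| Quarter effects by group | −0.04511, −0.04511 | 0.00261, 0.00261 |
| Common quarter effects plus a post term | −0.0394, −0.0396 | 0.00409, 0.00396 |
| Common quarter effects, no post term | −0.0368, −0.0369 | 0.00360, 0.00387 |

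In relative terms the influence changes by 0.00396/0.00409 − 1 ≈ −3% in the second row and by 0.00387/0.00360 − 1 ≈ +7% in the third. The shift is small and does not reliably go the helpful way.

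**Contrast: truncation at the within-group 99th percentile**, same data as simulation 1. In the order 2%, 5%, 16.7%:

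- The heaviest enrolee's share of enrolee weight fell from 14.3% to 2.5%, from 4.98% to 1.05%, and from 2.63% to 0.25%.
- Enrolee effective sample size rose from 36 to 107, from 148 to 265, and from 536 to 1,246.
- The clustered standard error fell in the second and third scenarios (0.0389 to 0.0328, 0.0186 to 0.0171) but rose in the first (0.0612 to 0.0662).

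Truncation bounds influence, but it does not improve every measure in every sample.

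**The case against.** **Weight-handling detail belongs in an analysis plan.** A truncation or trimming rule may stand in the full protocol or the statistical analysis plan, neither of which is shown. This stands. A reader might infer that the study has no such rule, but a condensed article cannot show that. The point is the property that the article positively assigns to stabilising.

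**The article claims a reduction, not a cure.** It also restricts eligibility before weighting, lists diagnostics, repeats them for subgroups and promises sensitivity analyses. This stands as evidence that the team does not regard the matter as closed. But diagnostics detect extreme weights without reducing their influence, and no named sensitivity analysis concerns the weights.

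**The exact identity depends on choices not stated.** The article gives neither the numerator nor the model equation. Calendar quarter is an exact matching variable in the WP1 Methods, so a quarter-specific numerator is conceivable, and that would not be one constant per group. This stands, and the conclusion is conditional accordingly. It does not rescue the sentence. In a separate simulation (100,000 patients, assumed slope 1.2 per SD), a quarter-specific numerator changed the largest-to-mean enrolee weight from 25.4 to 21.5 at 7.4% enrolled and from 35.9 to 37.7 at 16.7%.

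**No material harm is shown.** A reader might infer that a few atypical enrolees will drive the primary estimate. The documents do not support that. In one assumed scenario with 22,173 enrolees and a largest-to-mean weight of 22.0, the heaviest enrolee holds 22.0/22,173 ≈ 0.1% of enrolee weight. The top 1% hold 7.2%, and truncation at the 1st and 99th percentiles raises the effective share only from 45% to 49.8%. The 14.3% in the working comes from 382 enrolees and a steep assumed propensity. The article's own ratio, "Assuming effective 1:5 average weighting, this gives 19 million patient-months for analysis", is a planning assumption and not an observed enrolled share.

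**Conclusion.** The concern holds in a limited form. For a binary exposure with one baseline propensity per patient and a marginal numerator, stabilising does nothing to the influence of extreme weights in a group-by-period difference-in-differences. With shared quarter terms it does very little, and in either direction. The sentence in the Analysis section therefore attributes to the primary analysis a protection that it lacks.

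The algebra needs no assumption about the data beyond those conditions. The practical size of the problem does: it depends on the propensity distribution and the enrolled share, and the article gives neither. The simulated figures illustrate a range from an ordinary loss of efficiency to heavy dependence on one patient; they do not predict this study's result. Nor does the finding show that truncated weights must be primary. That is a trade of bias against variance on which statisticians may reasonably differ.

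**What to change.** 1. In WP1 Analysis, keep the statement that stabilised weights balance measured covariates. Delete the part about extreme weights, or attach it to a device that does bound influence.
2. Before outcomes are seen, pre-specify at least one bounded-weight version of the analysis, to be reported beside the untruncated estimate. Examples are truncation at a stated percentile within each exposure group, or overlap weights, noting that these change the target population. Which version is primary is the sponsor's choice, stated in advance.
3. Report effective sample size and the largest-to-mean weight separately for enrolees and comparators, not pooled, in the main and subgroup analyses.

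The cost is a few sentences and a small amount of extra analysis. The bounded-weight result will carry some residual imbalance (truncation) or answer for a different population (overlap weights). Showing it beside the untruncated estimate lets the reader see how much that matters.
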